**Fig. 2 Fig2:**
[figure not shown]
Sample size calculation

**Fig. 3 Fig3:**
[figure not shown]
Schedule of enrollment, interventions, and assessments*

### Adverse events

Adverse events refer to undesirable and unintended signs, symptoms, or illnesses that occur after the procedure of a clinical research process. Adverse events related to acupuncture treatment are harmful and unintended reactions that cannot be excluded from the causal relationship with acupuncture used in this study. The types of adverse events include subcutaneous hemorrhage (2.9%), autonomic nervous system abnormalities (1%) such as hypotension and excessive sweating, and gastrointestinal symptoms (< 1%) such as nausea and vomiting. Significant adverse events include those that cause death or threaten life, require an extension of hospitalization or length of stay, cause disability, impairment of function, or congenital malformations. Even if not in the circumstances listed above, a medical condition that is likely to have a significant impact on the patient’s well-being and health condition is regarded as a significant adverse event (SAE) by the medical judgment of investigators and relevant experts. All adverse events will be recorded in the Case Report Form, and SAEs will be reported to the IRB as well as on the ClinicalTrials.gov database, and managed appropriately. The IRB will decide whether to stop or continue this study when SAEs occur.

### Data management

Double checks for data values will be performed by a trained research assistant after completion of final data collection. A data and safety monitoring committee is not required since the acupuncture study has minimal risks. Periodic data monitoring and audit for the important aspects of the trial will be conducted by two independent, trained investigators. The final data will be assessed by the first author and independent statistician. An interim analysis is not planned. The information of patients discharged before day 5 will be collected from telephone or outpatient clinic at day 5, which will be included in the analysis. For those who died during the study, only the data before death are included in the analysis.

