### Outcomes

The primary endpoint is the change in Visual Analog Scale (VAS, 0–100) for pain on day 5 compared to pretreatment. Secondary endpoints include daily VAS (days 1–4), requirement of analgesics, changes of inflammatory marker (C-reactive protein), time to pain disappearance and hospital days. Daily VAS is the average of VAS measured three times a day. The requirement of analgesics includes both the amount and frequency of analgesics administered daily.

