### Statistical analysis

The statistical analysis will be based on the intention-to-treat (ITT) population. Missing data imputation will be used in order to evaluate the robustness of the primary endpoint analyses. The primary imputation method will be LOCF (last observation carried forward). The statistical analysis will be conducted for both three (EA 1: EA 2: control) and two (EA: control) groups. The null hypothesis is that there is no difference in the changes of variables between the two or three groups before and after treatment. The three groups will be compared by one-way analysis of variance (ANOVA) or the Kruskal-Wallis test for continuous variables, and chi-squared or Fisher’s exact test for categorical variables. Analysis of covariance will be performed with covariates that may affect VAS level. Post hoc analysis will be done if there is a significant difference between the three groups using the Bonferroni correction. The two (EA: control) groups will be compared by means of Student’s *t* test or Wilcoxon’s rank sum test for continuous variables, and chi-squared or Fisher’s exact test for categorical variables. A two-sided *P* value of less than 0.05 will be considered to indicate statistical significance.

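### Daily VAS and analgesic use between an early discharge and day 4 have no described source, and no rule is stated for those missing days

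*Protocol article*

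**What the plan says.** Four statements in the Methods bear on this point.

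- Outcomes, secondary endpoints: "Secondary endpoints include daily VAS (days 1–4"), scored by the rule "Daily VAS is the average of VAS measured three times a day".
- Outcomes, analgesics: "The requirement of analgesics includes both the amount and frequency of analgesics administered daily".
- Data management, early discharge (last word omitted): "The information of patients discharged before day 5 will be collected from telephone or outpatient clinic at day 5, which will be included in the". For deaths, the same section says which data are used: "For those who died during the study, only the data before death are included in the analysis".
- Statistical analysis: "Missing data imputation will be used in order to evaluate the robustness of the primary endpoint analyses". LOCF is the main method and the population is intention-to-treat. Continuous variables are compared by ANOVA or Kruskal-Wallis (three groups) and by t test or rank sum test (two groups), with an analysis of covariance for factors affecting VAS.

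The primary endpoint is separate: "The primary endpoint is the change in Visual Analog Scale (VAS, 0–100) for pain on day 5 compared to pretreatment". The planned day-5 contact serves it directly.

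**The concern.** The protocol expects some patients to go home before day 5. Once home, nobody is described as taking three VAS readings a day or recording which analgesics are used. The contact that is described comes on day 5, after the days in question.

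These missing days are unlikely to be a random subset. EA may stop once pain resolves, and time to pain disappearance and hospital days are both endpoints, so the protocol itself allows for recovery and length of stay to respond to treatment. If EA works as hypothesised, the arms will probably lose different numbers of patients before day 4, and those lost will tend to have low scores.

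The tests named in the Statistical analysis section use only patients who have a value. Applied to what is available on days 3 and 4, they would compare inpatients selected after randomisation by their recovery. The pain curve would also change population between day 4 (inpatients) and day 5 (everyone). The analgesic comparison on those days has the same weakness.

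**Working it through.** **1. The statements side by side**

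| Item | What the endpoint needs | What is described after discharge |
|---|---|---|
| Daily VAS, days 1–4 | three readings on each day | one contact, at day 5 |
| Analgesic requirement | amount and frequency for each day | nothing specific; the day-5 information is not itemised |
| Day-5 VAS (primary) | a value at day 5 | the day-5 contact |
| Missing-value rule | one for each endpoint with gaps | imputation tied to the primary endpoint |

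The first two rows do not fit together; the third does.

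**2. The plan's own figures.** The documents give no discharge rate and no expected VAS by day, so there is no stated figure for this point to reproduce. The planning SDs (19 test, 25 control) and the 20-point difference are used below. They give (19² + 25²)(1.960 + 1.282)²/20² = 25.9 evaluable patients per group, close to the stated 25. This has no bearing on the point.

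**3. Simulation inputs, all assumed except the SDs 19/25, the 20 points and the 0–100 scale**

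- Control means 60 before treatment, then 55, 47, 40, 33 and 27 on days 1–5.
- EA benefit of 20, 40, 60, 80 and 100% of 20 points on days 1–5, so the day-4 EA mean is 33 − 16 = 17 before truncation to 0–100.
- SDs 25/19, and common SDs of 15, 19, 22 and 25; AR(1) correlation 0.8.
- Discharge at the end of days 2–4 with probability 0.3–0.7 when VAS is at most 10 or 20. Day 2 therefore loses nobody. Roughly 5–30% of EA patients are gone before day 4.

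**4. Check of the true day-4 values.** For a normal score cut off at zero, the mean is μΦ(μ/σ) + σφ(μ/σ); the ceiling at 100 is negligible.

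- SD 22, EA: 17 × 0.780 + 22 × 0.296 = 19.8. Control: 33 × 0.933 + 22 × 0.130 = 33.6. Difference about 13.9.
- SDs 25/19, control: 33 × 0.907 + 25 × 0.167 = 34.1. EA: 17 × 0.815 + 19 × 0.267 = 18.9. Difference about 15.1–15.2.

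Both agree with the simulated truth.

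**5. Day-4 results**

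| Quantity | True | Reported | Shift |
|---|---|---|---|
| Difference, SD 22, inpatients only | 13.9 | 12.2–13.4 | −1.7 to −0.5 |
| Difference, equal SDs 15–25, inpatients only | about 13–15 | – | −2 to −0.4 |
| Difference, SDs 25/19, inpatients only | 15.1–15.2 | 15.4–15.8 | +0.3 to +0.6 |
| EA mean, SD 22, inpatients only | 19.7 | 21.2–25.7 | +1.5 to +6.0 |
| Difference, LOCF | 13.8–15.2 | – | shrinks by about 0.1 to 1.8 |

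Across all settings the EA mean is about 1–6 points too high with inpatients only, and control about 1–5. Because both arms lose low scores, much of the distortion cancels in the difference. A multivariate-normal likelihood fit using the earlier days and day 5 came within about 0.3 points of the true difference at all SDs tried.

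**6. Scale.** With 33 per arm, the standard error of a difference is 22 × √(2/33) = 5.4, or √((625 + 361)/33) = 5.5 with the planning SDs. A 2-point shift is 2/5.4 = 0.37 of a standard error; 0.6 is 0.6/5.5 = 0.11.

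**7. A harsher assumption.** Suppose everyone at or below a VAS of 5–20 that day is absent, with means 50 v 30 or 40 v 20 and SDs 25/19. Then 4–21% of control and 9–50% of EA patients are missing, and the difference falls from about 19–20 to 14–18. With the same SDs the sign is opposite to step 5, so the direction depends on the discharge pattern.

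**The case against.** The strongest reply is that a reader might infer three things that the article does not say.

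- *That early leavers are contacted only at day 5, so the missing days cannot be scored.* The word only does not appear. The information to be collected is not itemised, recall or a home diary is not excluded, and the assessment schedule (Fig. 3) is not shown. What can be said is that no source is described.
- *That the day 2–4 comparisons drop the best recoverers.* No such exclusion is stated. The population is intention-to-treat and LOCF is named. Imputation is tied to the primary endpoint, which leaves the secondary endpoints unspecified rather than fixed as complete-case. That early discharge marks good recovery is plausible but also unstated.
- *That the treatment comparison would be seriously distorted.* Under the assumed patterns of step 5 the shift is well under one standard error, and every driving input is assumed. The analgesic endpoint was not simulated.

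It can also be said that missing-data rules for secondary endpoints, and the choice of model, commonly sit in the SAP. That is fair for the analysis alone. It does not dispose of the point: the article itself fixes the scoring rule, the post-discharge contact and the scope of imputation. An SAP can choose an analysis, but it cannot restore readings or home doses that were never collected. Nor do an intention-to-treat population or LOCF remove the problem: the first supplies no scores, and the second shrank the difference in every scenario tried.

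One limit on the check: simulated discharge depends on recorded VAS, so the likelihood model's assumption was met by construction and its good recovery was expected.

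**Conclusion.** The point stands as a gap between the endpoint definitions and the stated follow-up, of minor to moderate weight and confined to secondary endpoints. As written, daily VAS and analgesic use from discharge to day 4 have no described source and no stated handling.

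Both obvious defaults carry some bias. With roughly 5–30% of EA patients gone before day 4, inpatients-only analysis moves the day-4 difference by about −2 to +0.6 points and LOCF shrinks it by up to about 1.8. The individual arm means, and the step from day 4 to day 5, are distorted more visibly than the difference. These sizes rest on assumed means, correlation and discharge rules; they illustrate the problem and do not predict the trial's result.

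A reader should not go on to infer that the primary result is biased by this route: day-5 data are planned for exactly these patients.

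**What to change.** Two changes.

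1. *Statistical analysis section:* analyse daily VAS with one likelihood-based repeated-measures model covering pretreatment, days 1–4 and day 5, with arm, day and arm-by-day terms, in all randomised patients. Early-discharged patients then contribute their inpatient days and their day-5 value. The primary day-5 analysis need not change for this reason.
2. *Data management section:* state that the day-5 contact already planned also records the analgesics (drug, amount, number of doses) taken on each day since discharge, and count these in the analgesic requirement.

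The cost is some analysis wording and a few questions in an existing contact. The second change should be made while the trial is still recruiting. The downsides are that the model assumes missingness depends on observed scores, and that home analgesic use is self-reported from recall. Daily calls after discharge are not proposed, because they need extra staff work for a modest gain.

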## Background

The prevalence of acute pancreatitis (AP) is increasing due to cholelithiasis and increased alcohol consumption [1]. While the overall mortality in all hospitalized patients with AP is approximately 10%, the mortality in the subset with severe AP may be as high as 30% [2]. AP causes significant abdominal pain, which can adversely affect patients’ quality of life. Most patients have associated nausea and vomiting [3]. Pain control for such patients is the mainstay of AP management.

Opioids are safe and effective for pain control in patients with AP. Compared with other analgesic options, opioids may decrease the need for supplementary analgesia [4]. However, frequent administration of opioid analgesics may result in opioid dependency [5, 6]. In the United States, there has been a tripling in the rate of opioid-related overdose deaths from 2000 to 2014, with over 28,000 deaths in 2014 [7]. This epidemic creates a dilemma for physicians who seek to provide adequate pain relief while minimizing risks of abuse and dependency [8]. Unfortunately, any innovative treatment for better analgesia than opioids has not been developed in medical science so far. Therefore, the development of a novel treatment for pain relief without triggering dependency is urgent.

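### The general rule for patients who die leaves in-hospital death uncounted as a bad outcome in the secondary endpoint hospital days; the effect is probably small and the repair is cheap

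*Protocol article*

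**What the plan says.** Four places in the protocol article bear on this.

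- **Data management.** "For those who died during the study, only the data before death are included in the analysis". The sentence names no endpoint and excepts none. It follows directly on the arrangement for obtaining day-5 information from patients who have already gone home.
- **Outcomes.** The secondary endpoints include "time to pain disappearance and hospital days". Nothing says how a stay that ends in death is counted.
- **Statistical analysis.** "The statistical analysis will be based on the intention-to-treat (ITT) population". Three-group comparisons use "one-way analysis of variance (ANOVA) or the Kruskal-Wallis test for continuous variables"; the comparison of pooled electroacupuncture (EA) with control uses Student's t test or Wilcoxon's "rank sum test for continuous variables". On imputation, "Missing data imputation will be used in order to evaluate the robustness of the primary endpoint analyses", so that text does not address hospital days.
- **Background and Exclusion criteria.** The Background says that "the overall mortality in all hospitalized patients with AP is approximately 10" per cent, and up to 30% in severe disease. The exclusion is limited to severe disease with multi-organ failure, so other severe cases may enter.

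**The concern.** Length of stay is cut short by two opposite events, recovery and death. An analysis that takes only the number of days treats them alike. With the pre-death rule applied as written, a death on day 3 gives a value of 3, which ranks ahead of a patient who recovers and leaves on day 8. The planned tests work on that raw value, and nothing in the Statistical analysis section treats death as a worst rank, a competing event or a failure to be discharged alive.

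What is at stake is how one secondary efficacy endpoint is read. If one arm has more early in-hospital deaths than another, its stay looks shorter for a reason that is not a benefit. The authors foresaw deaths, since they wrote a rule for them, but the rule does not suit this endpoint.

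**Working it through.** **1. Plan's own figures.** The plan computes nothing for hospital days. The only figure needed from it is the arm size. With a difference of 20 and SDs of 19 and 25, the pooled SD is √((19² + 25²)/2) = 22.2. At two-sided 5% and 90% power, n = 2 × (1.960 + 1.282)² × 22.2² / 20² ≈ 25.9, so 26 per arm against the stated 25. Allowing for 20% dropout, 26/0.8 = 32.5, so 33. The stated 33 per arm is used below, with 66 for the two EA arms pooled.

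**2. The two readings of the rule.**

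| Reading | Value for a patient who dies in hospital | Consequence |
|---|---|---|
| Literal | Days up to death | Death can rank ahead of recovery with a longer stay |
| No discharge, so no value | None | Survivors only; not all randomised patients are compared |

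Neither places death at the unfavourable end.

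**3. Effect of one death (assumed: death on day 3, stay otherwise 20 days).**

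- Literal reading, one arm: (20 − 3)/33 = 17/33 = 0.52 day off the mean.
- Literal reading, pooled EA: 17/66 = 0.26 day.
- Survivors-only reading, one arm whose mean would otherwise have been m: the mean falls to (33m − 20)/32. For assumed m = 7, 10 and 14 this is 6.59, 9.69 and 13.81, a fall of 0.41, 0.31 and 0.19 day. The direction is the same and the size smaller.

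**4. Set against sampling error.** No SD for stay is given. Assuming 5 to 10 days, the standard error of a 33 versus 33 difference is SD × √(2/33) = 1.2 to 2.5 days, so 0.52 day is about 0.2 to 0.4 standard errors.

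**5. Expected deaths.** The trial's mortality is unknown, so a range is assumed. Expected deaths among 99 patients are 99p, and the chance of at least one is 1 − (1 − p)^99.

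| p | Expected deaths in 99 | Chance of at least one |
|---|---|---|
| 1% | 1.0 | 63% |
| 3% | 3.0 | 95% |
| 5% | 5.0 | 99% |
| 10% | 9.9 | over 99.9% |

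**6. When the arms are distorted.** If survivors in both arms stay L days on average, deaths occur on day d, and early-death proportions are p₁ and p₂, the literal reading gives a difference in means of −(p₁ − p₂)(L − d). It is zero when p₁ = p₂, and it favours the arm with more deaths only when d < L. For 10% versus 3%, with L from 7 to 14 and d from 2 to 5, it runs from 0.07 × (7 − 5) = 0.14 to 0.07 × (14 − 2) = 0.84 day.

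**7. Rank-sum test, by simulation.** 3,000 trials per row, 66 EA versus 33 control, identical log-normal survivor stays with median 9 days and log-SD 0.5, all deaths on day 3. The table gives the share of trials that find a shorter stay under EA at one-sided 0.025.

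| Assumed deaths, EA vs control | Death scored at day 3 | Death ranked worst |
|---|---|---|
| 0% vs 0% | 2.3% | 2.3% |
| 5% vs 0% | 5.6% | 0.8% |
| 10% vs 3% | 7.6% | 0.5% |
| 10% vs 0% | 12.5% | 0.2% |

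The last three rows assume that mortality truly is higher under EA. They show the mechanism and are not a forecast.

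**The case against.** The best reply is that the sentence does not mention hospital days. Coming straight after the day-5 follow-up of discharged patients, it reads naturally as a rule for the pain scores. It does not say that a death is scored as a completed stay, and the article is a condensed account whose full protocol may define the endpoint. Part of this stands: a reader might infer that the plan definitely enters deaths as short stays, and the text does not settle that. But the rule is general and exempts nothing, and the alternative reading leads to a survivors-only comparison. The criticism is of a stated rule that reaches this endpoint, not of a missing definition.

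A reader might also infer that a handful of deaths could reverse the comparison. The documents do not support that. One death moves an arm mean by about 0.5 day, a fraction of a plausible standard error. The 10% figure is for all hospitalised patients, whereas multi-organ failure is excluded here and participants must be able to communicate and consent, so the trial's rate is plausibly well below it. Randomisation produces no systematic difference if expected mortality is equal, and nothing in the article suggests that EA raises mortality. Death is also a serious adverse event that must be recorded and reported, so deaths are not hidden, although a tabulation by arm is not stated.

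**Conclusion.** The point holds in a limited form. As written, the rule for patients who die leaves hospital days without a sound treatment of in-hospital death: such a death is either a short stay or absent from the comparison, and in neither case an unfavourable result.

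The consequence is confined to one secondary endpoint; the mechanism does not touch the day-5 pain endpoint or the sample size. A distortion between arms needs unequal early in-hospital deaths, and a death later than the usual stay would not count as short. The likely size is small: about 0.5 day per excess death in an arm of 33, or 0.26 day in the pooled 66. These figures rest on an assumed day of death and an assumed alternative stay, because the article gives no length of stay, no day of death and no mortality rate for the patients it enrols. This is an inexpensive improvement to the analysis wording, not a threat to the trial's main conclusion.

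**What to change.** Before outcomes are examined by arm, amend the Data management and Statistical analysis text along these lines:

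> The rule restricting analysis to pre-death observations does not apply to hospital days. Hospital days is the time from randomisation to discharge alive. Patients who die in hospital are kept in the comparison and given a rank worse than any observed stay, in the Kruskal-Wallis test for three groups and the Wilcoxon rank-sum test for EA versus control. The number of deaths in each arm is reported beside this endpoint.

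No new data are needed, since deaths are already recorded as serious adverse events, and both rank tests are already in the plan.

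There are costs. The endpoint becomes a ranking that combines death and stay, so ANOVA and the t test are no longer options for it. It is summarised by a median with deaths ranked worst, and mean stay can be given only descriptively for survivors. Other repairs, such as days alive and out of hospital over the 1-month follow-up, or time to discharge alive with death as a competing event, would also be acceptable. Worst rank is suggested because it departs least from the tests already named.

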### Statistical analysis

The statistical analysis will be based on the intention-to-treat (ITT) population. Missing data imputation will be used in order to evaluate the robustness of the primary endpoint analyses. The primary imputation method will be LOCF (last observation carried forward). The statistical analysis will be conducted for both three (EA 1: EA 2: control) and two (EA: control) groups. The null hypothesis is that there is no difference in the changes of variables between the two or three groups before and after treatment. The three groups will be compared by one-way analysis of variance (ANOVA) or the Kruskal-Wallis test for continuous variables, and chi-squared or Fisher’s exact test for categorical variables. Analysis of covariance will be performed with covariates that may affect VAS level. Post hoc analysis will be done if there is a significant difference between the three groups using the Bonferroni correction. The two (EA: control) groups will be compared by means of Student’s *t* test or Wilcoxon’s rank sum test for continuous variables, and chi-squared or Fisher’s exact test for categorical variables. A two-sided *P* value of less than 0.05 will be considered to indicate statistical significance.

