### Interventions and electroacupuncture procedures

Local EA is given in group EA 1, while local with distal EA is given in group EA 2, additionally. The EA 1 group receives the same SOC therapy in combination with EA therapy at a total of two acupoints including *Zhong Wan* (CV12) and *Shang Wan* (CV13). The EA 2 group also receives the same SOC therapy in combination with EA therapy at a total of 14 acupoints including *Zhong Wan* (CV12), *Shang Wan* (CV13), *He Gu* (LI4), *Nei Guan* (PC6), *San Yin Jiao* (SP6), *Xuan Zhong* (GB39), *Zu San Li* (ST36), and *Shang Ju Xu* (ST37) (Fig. 1) [14, 16, 17]. Electric stimulation is applied with mixed frequencies (30 and 3 Hz). Each EA session lasts 15 min (STN-330 electronic stimulator, Stra Tek Co., Ltd., Gyeonggi-do, Korea). Both EA groups receive auricular acupuncture therapy at a total of five auricular acupoints, including Sympathetic, *Shen Men*, Abdomen, Pancreas gall, and Spleen, alternately at the right or left side, whenever EA is given. Both EA groups undergo one session of EA daily from day 1 until day 4, or until pain resolves.

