### Planned number of subjects and period

A total of 99 patients will be enrolled for 2 years. Sample size calculation was performed for achieving a 90% power at the 5% level of significance.. The sample size was calculated as in Fig. 2. The population standard deviation (*σ*) was determined as the largest value according to a previous study [18]. Therefore, the standard deviations are 19 for the test group and 25 for the control group. The expected minimum clinical difference of 20 has been defined; this is the difference between the test group and the control group. This is achieved by enrolling 25 evaluable patients in each treatment group. To allow for a possible 20% dropout rate, 33 patients will be randomised to each group. The enrolled patients will be followed up for 1 month to monitor any delayed adverse events (see Fig. 3 for the schedule of enrollment, interventions, and assessments..

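### LOCF is the only imputation method named for day-5 pain, its role in the primary result is unclear, and it suits a falling pain score poorly

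*Protocol article*

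**What the plan says.** All references are to the protocol article.

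- **Outcomes:** "The primary endpoint is the change in Visual Analog Scale (VAS, 0–100) for pain on day 5 compared to pretreatment". Daily VAS on days 1 to 4 and time to pain disappearance are secondary endpoints.
- **Statistical analysis:** "The statistical analysis will be based on the intention-to-treat (ITT) population". Then: "Missing data imputation will be used in order to evaluate the robustness of the primary endpoint analyses". Then: "The primary imputation method will be LOCF (last observation carried forward"). No other imputation method is named.
- **Planned number of subjects and period:** the calculation rests on 25 evaluable patients per group, and "To allow for a possible 20% dropout rate, 33 patients will be randomised to each group".
- **Data management:** patients who leave hospital early are contacted at day 5 by telephone or at a clinic visit, and the values so obtained are analysed. On deaths: "For those who died during the study, only the data before death are included in the analysis".
- **Interventions and electroacupuncture procedures:** "Both EA groups undergo one session of EA daily from day 1 until day 4, or until pain resolves".
- **Randomization:** treatment is open-label after allocation.

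**The concern.** LOCF assumes that a patient's pain would have stayed at its last recorded level until day 5. The protocol points to falling pain: EA sessions may stop early because pain has gone, and time to pain disappearance is an endpoint. A patient lost early would then usually be scored at day 5 with a value that is too high. Single imputation also treats that value as if it had been measured, so its uncertainty is ignored.

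The role of LOCF is not settled either. The robustness sentence points to a sensitivity analysis. The ITT sentence, together with the label of primary imputation method, points to the main analysis. At stake is the estimate on which the superiority claim rests. With patients and staff aware of the allocation, the amount and timing of dropout could differ by arm, and LOCF would turn that difference into part of the estimated treatment effect.

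**Working it through.** **1. The plan's own figure.** Inputs from Planned number of subjects and period: difference 20, SDs 19 and 25, power 90%, 5% level (two-sided, from Statistical analysis).

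- Common SD = √((19² + 25²)/2) = √493 = 22.2.
- n per group = 2 × [22.2 × (1.960 + 1.282)/20]² = 25.9, so 26 against the stated 25.
- With 20% dropout, 26/0.8 = 32.5, so 33. The stated 33 reproduces.
- 20% of 33 is 6.6, so the plan allows for about 6 or 7 patients per group without an evaluable outcome.

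**2. Effect of LOCF on an arm mean.** Let c be the true mean change at day 5, d the share of patients imputed, and f the fraction of c already reached at the last observation. The expected LOCF mean is c × [(1 − d) + d × f].

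The documents give no values for c, f or the split of d between arms. The figures below are assumptions, shown as a range: c = −50 (EA) and −30 (control), a true difference of 20, with f = 0.25, 0.50 and 0.75. Power is for one EA arm against control, 33 per arm, SD 22.2, standard error 22.2 × √(2/33) = 5.5. It is 95.5% at the full 20 points.

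| Dropout EA / control | LOCF difference at f = 0.25 / 0.50 / 0.75 | Bias | Power |
|---|---|---|---|
| 20% / 20% | 17 / 18 / 19 | −3 / −2 / −1 | 87.5% / 90.9% / 93.5% |
| 10% / 30% | 23 / 22 / 21 | +3 / +2 / +1 | 98.8% / 98.1% / 97.0% |
| 30% / 10% | 11 / 14 / 17 | −9 / −6 / −3 | 52% / 73% / 88% |

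Example, first row at f = 0.25: EA −50 × 0.85 = −42.5; control −30 × 0.85 = −25.5; difference 17.

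With equal d and f the loss is d × (1 − f) × 20, whatever the two means are. With unequal dropout it does depend on them. Across −60/−40, −50/−30 and −40/−20, the 10%/30% split gives +0.5 to +4.5 and the 30%/10% split gives −10.5 to −2.5.

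**3. No true effect (both arms −40, assumed).** Equal dropout and timing give a difference of 0. A 10%/30% split gives a spurious 6 / 4 / 2 points. With d the spurious difference, the rejection rate 1 − Φ(1.96 − d/5.5) + Φ(−1.96 − d/5.5) is about 0.195 / 0.113 / 0.065. A 15%/25% split gives 3 / 2 / 1 points and 0.085 / 0.065 / 0.054. These rates keep the SD at 22.2 and so are approximate.

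**4. The same effect in daily terms (assumed falls of 5, 10 or 15 points per day).** A patient last seen on day 2 is overstated at day 5 by 3 × 5, 3 × 10 or 3 × 15 = 15, 30 or 45 points. A dropout gap of 10 percentage points then gives 1.5, 3.0 or 4.5 points, about 8% to 23% of the 20-point target. If dropout is 20% in both arms but falls on day 1 in one and day 3 in the other, a 10-point daily fall gives 0.2 × (40 − 20) = 4 points.

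**The case against.** The strongest reply is that LOCF may not touch the primary result at all. The robustness sentence read alone gives imputation a sensitivity role, and powering on evaluable patients with dropouts added on top fits that reading. LOCF would then already be where a reviewer would put it. This stands as a reason not to call the primary contrast biased. It does not remove the need to clarify, because the ITT sentence points the other way.

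Second, day-5 contact with patients discharged early removes a likely cause of missing values. Where pain has already gone, carrying a near-zero score forward does little harm. This also stands: only withdrawals and failed contacts remain, so one cannot assume that the full 20% would be imputed with a harmful value.

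Third, at equal dropout and timing the error is conservative for a superiority claim, and the documents give no reason to expect an imbalance in a particular direction. The 1.5 to 4.5 points in step 4 are below one standard error (5.5), and a straight-line fall ignores the floor at zero. These points limit the size of the problem but do not make LOCF a good lead method.

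A reader might also infer that a patient who dies is scored at day 5 as alive with stable pain. The Data management section does not say so. It says only that data up to death are used, which is equally compatible with such a patient having no day-5 value. Deaths by day 5 should be few, since severe disease with multi-organ failure is excluded.

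Finally, covariance structure and similar model detail commonly belong in an analysis plan, which is not shown, and their absence here is no fault.

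**Conclusion.** The point holds in a limited form and should be fixed. The article commits to LOCF as its lead and only imputation method and leaves open whether that method produces the primary result. If it does, the expected consequence at the planned 20% dropout, equal across arms in amount and timing, is a loss of about 1 to 3 of the 20 points and no bias under the null. If dropout differs by arm, the bias can go either way: about 1.5 to 4.5 points for a 10-percentage-point gap under the assumed daily falls, and from +3 to −9 points for a 20-percentage-point gap with mean changes of −50 and −30.

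All of these sizes rest on assumed trajectories, dropout splits and timing. The stronger reading, that the day-5 contrast will be biased, is not supported: the documents fix neither the use of LOCF in the primary analysis nor any imbalance in dropout.

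**What to change.** - State that the primary day-5 contrast comes from a method valid under missing at random that uses the daily VAS already collected. A mixed model for repeated measures with baseline VAS would do; so would multiple imputation.
- Reword the robustness sentence so that the main analysis and the sensitivity analyses are named separately.
- Keep LOCF, if at all, as a sensitivity analysis beside a delta-adjusted one.
- State how the few patients who die before day 5 enter the day-5 analysis.

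The cost is revised wording and a little more programming, with no new data. The drawback is reliance on the missing-at-random assumption, which the delta-adjusted analysis is there to test. The change should be made before the data are analysed.
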